## 2.2.6. Interventions

For the purpose of standardization and in line with current practice, in both groups code status discussions will take place upon hospitalization. Residents allocated to the intervention group will participate in a communication workshop, where they will receive detailed instructions about the shared decision-making checklist including specific communication teachings. Additionally, residents will be asked to use a

Figure 2. CLEAR Checklist

### CLEAR Checklist

#### 1 Clinician-Patient Engagement

Initially explain to the patient that...

- Code status discussions are done routinely with all patients – even if a cardiac arrest is not expected
- The code status does not have any influence on the ongoing treatment
- Disclose that a decision needs to be made
- The decision will be documented in the medical records
- Formulate the equality of partners, i.e. patient participates in the decision-making

#### 3 Explore Patient Preferences

- Investigate patient's understanding, expectations, health beliefs, quality of life
- Explore patient's preference, identification of both parties' preferences
- Decision-making, negotiate resuscitation measures if necessary (resuscitation, intubation, intensive care)
- Reach a shared decision

#### 2 Learn & Inform

- Explore if the patient has already thought about his/her code status
- Summarize what the patient has said and announce further information/explanation
- Provide information and explain therapeutic options on treatment or management in case of a cardiac arrest:

##### a) Life-sustaining treatments: Cardiopulmonary resuscitation ("Full Code Status")

- Chest compressions (see decision aid)
- Ventilation/intubation
- Medication for resuscitation and circulatory stabilization
- Benefits:** Patient may be successfully resuscitated
- Risks:** Prognosis is often poor (most patients die despite resuscitation or develop neurological impairments), fractured ribs

##### b) Alternative: Forgoing life-sustaining measures and focusing on a palliative care ("Do-Not-Resuscitate Order", DNR)

- Strategy (alleviation of suffering, e.g. pain, shortness of breath)
- Benefits:** Less suffering, discomfort, and complications
- Risks:** Patient will most likely die

#### 4 Assess & Document

- Document the shared decision (resuscitation/intubation/intensive care) in the electronic medical record
- Explain that the decision can be changed at any time

#### 5 Review Advance Directive

Ask if the patient has an advance directive – and make sure it is documented in the electronic medical record

[figure not shown]
[figure not shown]
[figure not shown]

[figure not shown]
[figure not shown]
[figure not shown]
[figure not shown]
[figure not shown]
[figure not shown]
[figure not shown]
[figure not shown]
[figure not shown]
[figure not shown]
[figure not shown]
[figure not shown]
[figure not shown]
[figure not shown]
[figure not shown]
[figure not shown]
[figure not shown]
[figure not shown]
[figure not shown]
[figure not shown]
[figure not shown]
[figure not shown]
[figure not shown]
[figure not shown]
[figure not shown]
[figure not shown]
[figure not shown]
[figure not shown]
[figure not shown]
[figure not shown]
[figure not shown]
[figure not shown]
[figure not shown]
[figure not shown]
[figure not shown]
[figure not shown]
[figure not shown]
[figure not shown]
[figure not shown]
[figure not shown]
[figure not shown]
[figure not shown]
[figure not shown]
[figure not shown]
[figure not shown]
[figure not shown]
[figure not shown]
[figure not shown]
[figure not shown]
[figure not shown]
[figure not shown]
[figure not shown]
[figure not shown]
[figure not shown]
[figure not shown]
[figure not shown]
[figure not shown]
[figure not shown]
[figure not shown]
[figure not shown]
[figure not shown]
[figure not shown]
[figure not shown]
[figure not shown]
[figure not shown]
[figure not shown]
[figure not shown]
[figure not shown]
[figure not shown]
[figure not shown]
[figure not shown]
[figure not shown]
[figure not shown]
[figure not shown]
[figure not shown]
[figure not shown]
[figure not shown]
[figure not shown]
[figure not shown]
[figure not shown]
[figure not shown]
[figure not shown]
[figure not shown]
[figure not shown]
[figure not shown]
[figure not shown]
[figure not shown]
[figure not shown]
[figure not shown]
[figure not shown]
[figure not shown]
[figure not shown]
[figure not shown]
[figure not shown]
[figure not shown]
[figure not shown]
[figure not shown]
[figure not shown]
[figure not shown]
[figure not shown]
[figure not shown]
[figure not shown]
[figure not shown]
[figure not shown]
[figure not shown]
[figure not shown]
[figure not shown]
[figure not shown]
[figure not shown]
[figure not shown]
[figure not shown]
[figure not shown]
[figure not shown]
[figure not shown]
[figure not shown]
[figure not shown]
[figure not shown]
[figure not shown]
[figure not shown]
[figure not shown]
[figure not shown]
[figure not shown]
[figure not shown]
[figure not shown]
[figure not shown]
[figure not shown]
[figure not shown]
[figure not shown]
[figure not shown]
[figure not shown]

More than 80 out of 100 patients die despite resuscitation in the hospital

Approximately 8 out of 100 resuscitated patients survive with significant neurological impairment

Approximately 12 out of 100 resuscitated patients survive and can live an independent life

| How important is it that you... | Not Important |   |   | Very Important |   |   | Option to consider if this is important to you |
|---------------------------------|---------------|---|---|----------------|---|---|------------------------------------------------|
| ... Stay alive longer?          | 0             | 1 | 2 | 3              | 4 | 5 | ✓ Have CPR                                     |
| ... Avoid serious brain injury? | 0             | 1 | 2 | 3              | 4 | 5 | ✗ Decline CPR                                  |

structured checklist for shared decision-making and a decision aid (see Figure 2), depicting a simulated CPR and a mechanically ventilated patient on an intensive care unit, as well as addressing prognostic data and outcomes of resuscitation. The decision aid from our study is based on previously published data and partially adapted from other decision aids that are registered in the Ottawa decision aid inventory[47]. To create the checklist, we grouped aspects of shared decision-making into five categories, from which we generated the acronym "CLEAR" (Clinician-Patient Engagement, Learn and Inform, Explore Patient Preferences, Assess and Document, Review Advance Directives). During the one-hour workshop, which was previously pilot-tested, residents randomized to the intervention group receive a teaching about shared decision-making including use of the checklist and decision aid, and will have to conduct a code status discussion with a simulated patient using the checklist and the decision aid. A member of our study team then will provide critical feedback how to facilitate the use of checklist and decision aid.

To accomplish fidelity to the intervention, the member of our study team who conducted the workshop and is not involved in the patient surveys, will accompany the resident for at least three code status discussions. Each time, we will provide feedback to residents regarding the discussion and – if necessary – a short rehearsal of single components of the training. To reduce bias, medical residents in the control group will also receive information about the importance of code status discussions and a general communication training (e.g., information structuring, responding to emotions) but no teaching regarding shared decision-making and no checklist or decision aid will be used. Communication workshops will be conducted before the resident will start conducting code status discussions, by members of our study team that will not have further contact with physicians and patients to improve blinding to group allocation.

#### **2.2.7. Patient involvement**

A total of 25 patients hospitalized on the medical wards of the University Hospital of Basel, as well as 15 healthcare providers (physicians and nurses) with experience in end-of-life care and emergency/intensive care medicine were involved in the design of the study and intervention as well as the review of the study protocol. To design the trial, patients and healthcare providers helped us in prioritization and selection of outcomes. Patients were asked for priority focus of this study. To design the intervention, input was sought from patients and healthcare providers. Especially, the decision aid was shown to patients to ascertain whether the depicted medical images or information would raise discomfort. Additionally, the decision aid and checklist were adapted according to inputs from clinical experts.

#### **2.2.8. Primary and secondary endpoints**

This trial is designed to investigate whether checklist-guided shared decision-making influences patients' decision regarding DNR code status, and at the same time improves decision-making quality. The primary outcome is thus the frequency of DNR code status among patients per resident (i.e., patients choosing that CPR and intubation measures should not be performed in case of acute deterioration). To ascertain the final code status decision, we will look at the code status documented in the medical chart. Code status decisions will be defined as "yes" (preference for CPR) and "no" (DNR).

As patients in our previous survey also prioritized the ability to make a reasonable decision, we have chosen patients' decisional conflict and comfort with the chosen code status as the key secondary endpoint, assessed through the validated German translation of the Decision Conflict Scale. The Decisional Conflict Scale is a validated questionnaire widely known to measure patients' uncertainty in choosing between treatment options, modifiable factors associated with this uncertainty as well as perceived effective decision-making. Further outcomes of interest mentioned by patients and healthcare providers were included as secondary outcomes and are detailed below.

**Additional secondary endpoints** are defined as follows.

1. Patient-associated outcomes

- a) Patients' knowledge about resuscitation measures and expected outcome of an in-hospital cardiac arrest. Knowledge will be defined as a score ascertained by a knowledge questionnaire that was adapted from previous studies [48, 49] and translated into German. The questionnaire of this study contains 6 questions regarding CPR and its prognostic outcome. Every correct answer given by the patient will add up to a score (between 0 and 6). State of not knowing the answer will be rated as a wrong answer.
- b) Patients' involvement in the decision-making process will be assessed through the PEF-FB-9, a validated German translation of the SDM-q-9 questionnaire[50]. The SDM-q-9 questionnaire is a well-established tool to measure quality of shared decision-making
- c) Patients' concerns and fears brought up by the resuscitation discussion: Specifically, we will assess the following dimensions: (1) disturbance caused by the discussion, (2) fear of suffering from an actual cardiac arrest, (3) fear of suffering from a life-threatening disease (4) perceived feeling of being put under pressure during discussion; each of them rated on a VAS (0-10).
- d) Patients' satisfaction and perceived overall quality of the code status discussions: Specifically, we will focus on the following dimensions, each rated on a VAS (0-10): (1) overall satisfaction with resuscitation discussion; (2) perceived transparency of the discussion; (3) comprehensibility of the medical information regarding a resuscitation process and measures; (4) how well resuscitation options were elucidated

2. Physician- associated outcomes

- a) Perception of the physician with the resuscitation discussion: Specifically, perceptions will be assessed for both study groups separately in regard to the following dimensions: (1) satisfaction with resuscitation discussion and self-confidence during the discussion, each rated on a VAS (0-10); (2) perceived time management of the discussion, rated on a VAS (0-10)
- b) Surprise question to identify patients at risk of death within the next 12 months

3. Documented results in Database after 30 days

Database assessment after 30 days: Specifically, we are interested in (1) length of stay; (2) number of ICU admissions; (3) number of re-admissions to the hospital; (4) 30d mortality

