There are several challenges to the current practice of code status discussions. First, these discussions are complex as objective medical facts and personal perspectives of physicians and patients both need to be integrated in the communication. Second, several studies found code status discussions to be ineffective due to poor communication skills of physicians[14, 15], which is particularly true for inexperienced residents[16]. Code status discussions are often conducted in a non-personalized way, missing the chance to focus on patients' values and goals[17]. Insufficient time during patient encounters pose an additional barrier for optimal communication[18-20]. Furthermore, the decision-making during code status discussions is often challenged by uncertainty around interventions and therapies that might be available, but whose outcomes remain uncertain[21, 22].

Importantly, patients with in-hospital cardiac arrests have a poor prognosis with a survival to hospital discharge rate of less than 20%[23, 24]. Furthermore, 40% of survivors suffer from substantial neurologic

deficits limiting their possibility to live an independent life[25]. In 2012, a British multi-center cohort study investigated medical charts of patients that had undergone resuscitation of an in-hospital cardiac arrest[26]. In more than 75% of patients that received CPR, the code status was unknown and 67% of patients that were resuscitated, actually had an underlying pre-existing fatal disease. Importantly, an independent assessment of all cases found that a DNR status would have been appropriate in 85% of cases, because the risk / benefit ratio was unfavourable for the patient, indicating medical futility. In addition, a recent cancer study shows that physicians often rather document a presumed code status, than conduct a discussion, leading to a high proportion of full code status despite severe illnesses of a patient [27]. Almost a third of patients that were presumably documented as full code would have preferred DNR code status[27].

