### **2.2.3. Patient population, inclusion, and exclusion criteria**

Residents on the medical wards will be the primary level of randomization. We have no exclusion criteria for physicians except if they refuse participation. Outcomes will be assessed in patients treated by these physicians. Any adult (>18 years) patient that is admitted for in-hospital care will be eligible. There will be no exclusion based on the type of illness, comorbidity or severity of illness in order to include a representative population of patients in Swiss hospitals. We will exclude patients unable to complete questionnaires or unable to follow code status discussions due to (1) intoxication, (2) paracsis; (3) serious psychiatric conditions (e.g., psychosis, depression with suicidal tendency, stupor), (4) cognitive impairment (e.g. dementia, delirium). Also, patients prior included in this study (i.e., patients who are hospitalized for the second time) are not eligible. Patients, in whom resuscitation attempts would be futile, will not be included in this study.

Recently Ebell et al developed the GO-FAR score, a clinical risk score to predict the estimated likelihood of neurologically intact survival of patients after in-hospital resuscitation[41]. The authors developed a multivariate prediction model based on 51`240 patients who experienced in-hospital cardiac arrest and calculated cut-off scores indicating likelihood of functional survival. The two lowest categories represent very low (<1%) and low (1-3%) likelihood of survival. It has therefore been suggested that these patients should be considered futile regarding CPR attempts [42]. Another tool to assess whether patients are at increased risk for poor outcome is the Clinical Frailty Scale[43]. This 9-category scale combines cognitive and physical aspects of frailty such as comorbidity, cognitive impairment, and disability. Research has shown that the scale, which is increasingly used in routine screening of older patients, predicts short-term mortality[44, 45]. However, the prevalence of futility in hospitalized patients upon admission assessed through the GO-FAR score and the Clinical Frailty Scale has not been systematically investigated.

According to the literature, we will define futility as a GO-FAR score  $\geq 14$  or patients in categories 7-9 in the Clinical frailty scale.

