#### **Figure 1. Study flow**

[figure not shown]

Baseline data will be entered into a centralized web-based study software (SecuTrial®) provided by the Clinical Trial Unit (CTU). The following baseline-data will be recorded for each patient:

- Socio-demographics (e.g., age, gender, socio-economic status, religion,)
- Health-related quality of life defined by EQ-5D (EuroQol)[46]
- Medical situation (i.e., complete list of main diagnosis and comorbidities)

To enable blinding of patients and physicians regarding the intervention and main endpoint of our trial, we will not share any detailed information, but ask for their participation in a trial comparing two different communication strategies on the quality of code status discussions. Yet, blinding of the study coordinator is not feasible. After code status discussion, a member of our research team will interview patients and residents separately. Using a structured questionnaire, patient outcomes and perceived quality of care as defined below (2.2.8. primary and secondary endpoints) will be assessed. In addition, the physician's perception of the code status discussion will be examined using a structured questionnaire.

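### The primary outcome is read from the chart, but the code status and advance directive that the patient already had are neither recorded nor adjusted for

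*Combined protocol and SAP*

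**What the plan says.** Section 2.2.8 defines the primary outcome as the frequency of DNR status per resident, meaning "patients choosing that CPR and intubation measures should not be performed in case of acute deterioration". The source is the record: "To ascertain the final code status decision, we will look at the code status documented in the medical chart". The coding has two values, for or against CPR. No time of reading is given, no rule requires the entry to come from the trial discussion, and there is no category for a presumed or carried-over entry.

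The baseline list in section 2.2.5 (below Figure 1) covers socio-demographics, EQ-5D, and diagnoses with comorbidities. The adjustment set in section 2.3.9 is age, gender and main diagnosis, with hospital as a further level. Neither names an existing code status or advance directive. The only exclusion tied to an earlier stay (section 2.2.3) concerns this trial itself: "Also, patients prior included in this study (i.e., patients who are hospitalized for the second time) are not eligible".

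The CLEAR checklist (Figure 2) touches on the subject. Step 2 explores whether the patient has already considered code status, step 4 has the decision documented, and step 5 says "Ask if the patient has an advance directive" and has the directive recorded. Section 2.2.6 states that controls use neither checklist nor decision aid, and that the discussion takes place on hospitalisation in both groups.

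**The concern.** The trial asks whether the discussion changes what patients decide. A patient may arrive with a DNR order from an earlier admission, with an advance directive, or with a status entered before anyone has spoken to them. Such a patient is eligible, and the chart entry counts whether or not the discussion altered it.

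The protocol itself gives reason to doubt that a chart entry always reflects a choice. Section 2.1 cites a study in which "physicians often rather document a presumed code status, than conduct a discussion", and reports that almost a third of patients presumptively documented as full code would have preferred DNR.

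Three things are at stake. Prior status is likely to be a strong predictor of the outcome, and leaving it out gives up precision. Any imbalance in it, by chance or because patients are identified after residents are randomised, goes unadjusted. Finally, a higher charted DNR rate could mean that more patients changed their decision or that more existing wishes reached the chart, and the planned data cannot separate the two.

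**Working it through.** **1. Where prior status could enter the plan**

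- Exclusions (2.2.3): earlier inclusion in this trial only.
- Baseline data (2.2.5): not listed.
- Adjustment set (2.3.9): not listed.
- Outcome definition (2.2.8): no reading time and no link to the discussion.
- 30-day data: changes in code status are listed for the parallel futility project (2.4) but not for the main trial (2.2.8).
- CLEAR step 5: the directive goes into the clinical record. It is a checklist prompt in the intervention arm, made during the discussion and not named as trial data, so it cannot serve as a baseline variable.

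**2. The plan's own sample size (2.3.10)**

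Inputs: 30% vs 45%, power 80%, alpha 0.05 (taken as two-sided), ICC 0.5, 15 patients per resident.

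- n per arm = [1.960·√(2·0.375·0.625) + 0.842·√(0.30·0.70 + 0.45·0.55)]² / 0.15² = 162.3, rounded up to 163.
- Design effect = 1 + 14·0.5 = 8, so 163·8 = 1304 per arm. 1304/15 = 86.9, rounded up to 87 residents per arm.
- Total: 174 residents and 2610 patients, with power 80.2%. The stated figures reproduce and are not in dispute.

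**3. Chance imbalance in prior DNR**

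Assumption: a share of patients arrives with a DNR order and keeps it. The documents give no share. With 1305 patients per arm:

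- Share 20%, no clustering: SE = √(2·0.20·0.80/1305) = 1.6 points.
- Share 20%, assumed ICC 0.05 for prior status: design effect 1.7, SE = 1.57·√1.7 = 2.0 points.
- Share 15%, no clustering: SE = √(2·0.15·0.85/1305) = 1.4 points.

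To keep the overall control rate at 30%, the rate r among the rest solves 0.30 = share + (1 − share)·r. This gives r = 0.125 at 20% and r = 0.176 at 15%. An imbalance d shifts the result by d·(1 − r). A one-SE imbalance therefore shifts it by 1.57·0.875 = 1.4 points (20%), 2.04·0.875 = 1.8 points (20%, ICC 0.05) or 1.40·0.824 = 1.2 points (15%).

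For scale, the SE of the planned comparison is √(0.4575/163.1) = 5.3 points at ICC 0.5. At ICC 0.1 the design effect is 2.4 and the SE is √(0.4575/543.75) = 2.9 points. Prior DNR alone is thus a modest part of the error at the planned ICC and a larger part if the ICC proves lower.

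**4. Power, if the 15 points apply only to patients without a fixed decision**

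Assumption: a share f does not change, the control rate stays at 30%, and the difference is 0.15·(1 − f).

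| f | Difference (points) | Power, ICC 0.5 | Power, ICC 0.1 |
|---|---|---|---|
| 0% | 15.0 | 80.2% | 99.9% |
| 10% | 13.5 | 71.7% | 99.6% |
| 20% | 12.0 | 61.8% | 98.5% |
| 30% | 10.5 | 51.0% | 95.3% |

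If the 30% and 45% already describe all admitted patients, including those with earlier decisions, none of this loss applies. Section 2.3.10 attributes the rates to pilot data in this population and does not say which patients were counted.

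**5. Changed decisions or better-recorded wishes**

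Assumption: true DNR preference is 30% in both arms, and a default full-code entry replaces the patient's wish in 20% of control charts and 5% of intervention charts. The charts then show 0.30·0.80 = 24% and 0.30·0.95 = 28.5%, a 4.5-point difference with no change in preference. If the default share is the same in both arms, the difference is zero. The documents do not say where in this range the trial lies.

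**The case against.** A reader might infer that decisions made before the trial are credited to the intervention and bias the result. The documents do not support that. Residents are randomised 1:1 within site and the same chart rule applies to both arms, so earlier decisions are expected to balance. Chance imbalance is already covered by the type I error, and a large one is improbable: at a 20% share, 5 points is 5/1.57 = 3.2 SE without clustering and about 2.4 SE at ICC 0.05.

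Selection is also restrained. Patients are consecutive, admissions are checked against the hospital database and bed-manager lists, the study team judges eligibility, and the primary endpoint needs no patient consent.

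It is also tempting to read the absence of a control checklist as meaning that control residents neither ask about directives nor document decisions. The plan does not say so. Controls hold the discussion on hospitalisation too, and are taught why it matters. They lack the prompt, not necessarily the practice.

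Patients with a presumed status are not beyond the intervention's reach either. They are among those it is meant to help, and bringing unrecorded wishes into the chart can fairly be called part of its purpose.

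These arguments stand against a claim of bias. They do not supply the missing baseline value, and they do not let the analyst say which mechanism produced a difference.

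**Conclusion.** The point holds as a gap in precision and interpretation. The primary outcome has no recorded baseline value, no stated reading time and no link to the discussion. The randomised comparison remains valid without these.

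The size cannot be derived from the documents, because every share used above is an assumption. Within those assumptions, typical chance imbalance is worth 1 to 2 points. The effect on power runs from none, if the planned rates cover all admissions, to a fall to 51% with 30% fixed decisions at ICC 0.5. The interpretive gap needs no assumed share: section 2.1 casts doubt on charted status as a measure of choice, and the checklist prompts documentation in one arm.

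**What to change.** - **Section 2.2.5, baseline data:** at the eligibility check, before the discussion and identically in both arms, the study team records from the chart the existing code status (none / full code / DNR) and whether an advance directive is present (yes/no). The plan does not say that this check always precedes the discussion, so the order should be stated.
- **Section 2.2.8:** fix when the chart is read, after the discussion and at the same point in both arms.
- **Section 2.3.9:** add prior status to the adjustment set of the primary model, and pre-specify a supportive analysis in patients with no prior status.
- **Optional:** in the interview already planned after the discussion, ask which status the patient chose and compare it with the chart. This should remain a sensitivity analysis. It covers only patients who consent to the questionnaires, and section 2.1 reports that more than 60% of surveyed patients did not recall such a discussion.

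The cost is two chart items, one covariate and one supportive analysis. The study team already consults the hospital database and checks each patient, so no extra visit is needed. In a logistic model the odds ratio becomes conditional on prior status, which the report should state.
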